### Randomization

#### Sequence generation and allocation concealment mechanism

Within each disease group, families will be allocated randomly to the intervention group or the control group with an allocation ratio of 1:1. The Sealed Envelope application will be used to generate random allocation sequences: this is an online software application for randomizing patients into clinical trials [71]. The random allocation sequence will be generated and concealed from the employees in the project. The families will consecutively be allocated to each group. Two arms for the TBI group and two arms for the tSCI group will be created with 66 families in each disease-specific group. The randomization will be conducted in blocks of 22, which increases the likelihood that the intervention groups and the control groups will have the exact same number of participants, even in the case of recruiting fewer participants than expected. When entering the unique family ID number in Sealed Envelope, the application randomizes the family to either the intervention group or the control group.

#### Implementation and awareness of assignment

The project nurses will be responsible for identifying and recruiting families that meet the inclusion criteria. The random allocation sequence will be generated by the nurses using the online randomization procedure [71]. Families will complete the baseline questionnaires before randomization.

Because of the nature of the study, it will be clear to all participants and the neuropsychologist whether the families are allocated to the intervention group or the control group. It is not possible to blind the participants or the neuropsychologist to the group allocation. The nurses will collect the study data. The neuropsychologist and statistician performing the data analyses will not be involved in collection of data on the outcome measures. Thus, they will be blinded to the association between the data from the questionnaires and the group to which the families are allocated. The nurses who are responsible for the data collection will not participate in data analysis.

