#### Analytical methods

Data will be stored in a password-protected electronic database, REDCap [72], which is a web-application for building and managing databases. All participants will be assigned a unique trial ID number and all demographic data, and data from the files and questionnaires will be stored in the database to ensure quality of the data. The nurses will be responsible for this part of the data management process.

The following analyses will be conducted in each arm of the trial. First, the baseline level of the primary outcome, generic QoL data, will be compared between groups using one-way analysis of variance (ANOVA). If there are significant differences at baseline, we will adjust for these in the following analyses. Intention-to treat (ITT) analyses will be performed to examine the effect of the family intervention using repeated measures ANOVA (rANOVA), with “time” as the repeated measurement. The comparison between the intervention group and control group in each disease group will be the between-group factor. Baseline characteristics will be assessed and compared between groups using one-way ANOVA, and we will adjust for these characteristics if necessary.

Little’s Missing Completely at Random (MCAR) approach will be applied for analysis of group allocation and of disease group to investigate whether drop-outs or missing data are associated with one of these parameters. Data analysis will be completed using STATA.

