### Limitations and generalizability

The present study will have some limitations that should be addressed. First, the study will only include families, who are willing to participate. Consequently, some families, who would fulfill our inclusion criteria, will not be included. One could speculate which families will be willing to participate in the study. Will it be families, who need help and support, or families, who have the time and resources? If a family refuses to participate, the reason for refusal will be obtained. Furthermore, as participation will be voluntary, all family members have the right to withdraw their consent if they want to quit the project. One could speculate whether families allocated to the control group will be more likely to drop out compared to families in the intervention group, because of a great desire to receive help. However, as the family intervention is very intense and time-consuming, this can also affect the risk of drop-outs in the intervention group. Therefore, prior to the allocation the nurses will inform the families about the content of the intervention in both groups both orally and in writing.

Second, most patients included in the study will have been hospitalized for specialized neurorehabilitation due to a severe traumatic injury. However, patients with severe cognitive disabilities or severe aphasia will be excluded, as patients with such disabilities will not be able to participate fully in the family intervention. This will affect the generalizability of the study, as patients with the most severe injuries or sequela will be excluded.

Third, participants will be recruited from only two clinics in Denmark - one clinic for patients with TBI and one clinic for patients with tSCI. This warrants caution with respect to generalizing the results and could potentially limit the external validity. However, as the two clinics have an uptake area covering the whole eastern part of Denmark with a total of almost 2.6 million inhabitants [45], the representativeness and generalizability is expanded.

Finally, due to the study design, it will not be possible to blind the participants or the neuropsychologist to the allocation. However, the researchers responsible for statistically analysing baseline, post-intervention, and follow-up questionnaire data will not know to which group the families were allocated.

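### Analyst masking is claimed for a role, the neuropsychologist, that the protocol also says cannot be blinded to allocation

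*Protocol article*

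**What the plan says.** Under Implementation and awareness of assignment, the protocol article first says that "it will be clear to all participants and the neuropsychologist whether the families are allocated to the intervention group or the control group", and then that "It is not possible to blind the participants or the neuropsychologist to the group allocation". A little further on it says that "The neuropsychologist and statistician performing the data analyses will not be involved in collection of data on the outcome measures". The next sentence draws the conclusion: "Thus, they will be blinded to the association between the data from the questionnaires and the group to which the families are allocated".

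Limitations and generalizability repeats that "it will not be possible to blind the participants or the neuropsychologist to the allocation". It then offers as a counterweight that "the researchers responsible for statistically analysing baseline, post-intervention, and follow-up questionnaire data will not know to which group the families were allocated".

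On who delivers treatment, the section on the manualized family intervention has a trained neuropsychologist facilitate sessions 2–8. Table 1 has the neuropsychologist hand out the homework to families just randomized to the intervention. The Control group section assigns the psychoeducation session to an experienced neuropsychologist who has no part in the intervention groups.

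**The concern.** The masking of the analysis rests on a reason that does not support it. Staying away from data collection prevents a person from influencing how the questionnaires are filled in. It does nothing to erase what that person already knows about who was treated. The neuropsychologist is the one staff role that the document expressly says cannot be blinded, yet it is also named alongside the statistician in the sentence on data analysis and is included in the blinding claim.

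Little else in this trial masks the treatment comparison. The outcomes are self-report questionnaires, participants know their group, and the project nurses both randomize and collect the data. Masked analysis is what the limitations section puts forward against the unavoidable lack of blinding. The Analytical methods section leaves some judgement to the analyst, for example that "we will adjust for these characteristics if necessary". A statistical analysis plan may settle that choice. Until it does, such judgement is best exercised by someone who cannot see the arms. If the masking statement stands as written, it is also likely to be carried into the trial report.

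**Working it through.** No arithmetic applies. The check is whether the statements can all be true together.

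1. **What the neuropsychologist knows.** Implementation and awareness of assignment says that allocation is clear to this role and cannot be hidden from it. Limitations and generalizability says the same.
2. **How that knowledge arises.** It comes from delivering sessions 2–8 and from meeting families once they are randomized to the intervention (manualized family intervention section and Table 1). It does not come from collecting questionnaires.
3. **What is claimed.** Implementation and awareness of assignment claims blinding to the association between questionnaire data and group. The limitations section claims more: that those analysing the "questionnaire data will not know to which group the families were allocated".
4. **The ground given.** The only ground is that the two roles do not collect outcome data. By step 2, removing data collection leaves the source of the knowledge untouched, so the inference fails for the neuropsychologist.

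The possible readings are then:

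- **Both roles analyse, and the neuropsychologist is the treating one.** The limitations claim is then untrue for that analyst, because the sentence before it says this role cannot be blinded.
- **Only the statistician analyses.** The limitations claim may hold, but the earlier section still includes the neuropsychologist in the blinding statement, on a ground that does not supply it.
- **The analyst is a third, uninvolved neuropsychologist.** The claim could then be true, but no section says so. The text uses the same term throughout without distinguishing persons. The second neuropsychologist it does describe, who runs the control session, knows which families are controls.
- **Only the link between record and arm is hidden.** This is coherent for someone who knows the allocation, provided that records cannot be traced to families and arms are coded. Analytical methods mentions a unique trial ID number but no coded arms, and this reading does not meet the stronger limitations claim.

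Each reading calls for a change of wording in at least one of the two sections.

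**The case against.** The best counter-argument is that blinding to allocation and blinding to the data–group association are different things. A therapist may know which families were treated and still be unable to tell which questionnaire record belongs to which arm. The logistics lean that way: nurses collect and manage the data, trial ID numbers are used, and the facilitator leaves the room while the post-intervention questionnaires are completed. This stands to the extent that the section on awareness of assignment, read alone, is not a strict contradiction. The firm conflict appears only when it is read with the limitations section, which claims that the analysts do not know the group.

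A second objection is that coding of arms and data exports belong in a data-management or analysis plan that is not shown. That is fair, and the absence of such detail from an article is not the point. The point is that the article asserts masking and gives a reason that does not establish it.

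Two stronger readings are tempting but not supported:

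- A reader might infer that one neuropsychologist treats every intervention family and so knows the allocation of the whole trial. The text speaks of a trained neuropsychologist for sessions 2–8 and never says that one person treats all families.
- A reader might infer that the statistician is unmasked too, because the Session Rating Scale and the Therapist Checklist Scale are completed only for the intervention arm. Nothing says that these variables are in the file the statistician receives.

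It also stands that masking the analyst would not cure unblinded self-report, which the article openly acknowledges.

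**Conclusion.** The concern holds for the neuropsychologist role. The document names two roles in connection with the data analyses and declares both blinded. For one of them the declaration does not follow from the reason given, and the limitations claim that analysts will not know the group is not supported. Nothing in the document shows that the statistician is unblinded.

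The size of any resulting bias cannot be derived, and none is asserted. The conclusion assumes that the term neuropsychologist refers to someone who delivers treatment wherever it appears without qualification. If an uninvolved analyst was meant, the claim may be true, but the text has to say so. The defect does not invalidate the trial. It should be corrected because the masking claim is used to offset an acknowledged weakness.

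**What to change.** In Implementation and awareness of assignment, replace the two sentences on analyst blinding with a statement along these lines: no neuropsychologist who delivers either arm takes part in the analysis of outcome data; the statistician analyses a dataset in which the arms are coded A and B until the primary analysis is complete. Delete the statement that the neuropsychologist is blinded. Align Limitations and generalizability so that the masking claim covers only the statistician working on coded arms.

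The cost is a change of wording and one export with the arm variable recoded. Trial status reports 13 families randomized, so the change can be made well before any analysis. The small downside is that the treating neuropsychologist cannot help with the primary analysis until the code is opened.

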#### Analytical methods

Data will be stored in a password-protected electronic database, REDCap [72], which is a web-application for building and managing databases. All participants will be assigned a unique trial ID number and all demographic data, and data from the files and questionnaires will be stored in the database to ensure quality of the data. The nurses will be responsible for this part of the data management process.

The following analyses will be conducted in each arm of the trial. First, the baseline level of the primary outcome, generic QoL data, will be compared between groups using one-way analysis of variance (ANOVA). If there are significant differences at baseline, we will adjust for these in the following analyses. Intention-to treat (ITT) analyses will be performed to examine the effect of the family intervention using repeated measures ANOVA (rANOVA), with “time” as the repeated measurement. The comparison between the intervention group and control group in each disease group will be the between-group factor. Baseline characteristics will be assessed and compared between groups using one-way ANOVA, and we will adjust for these characteristics if necessary.

Little’s Missing Completely at Random (MCAR) approach will be applied for analysis of group allocation and of disease group to investigate whether drop-outs or missing data are associated with one of these parameters. Data analysis will be completed using STATA.

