##### Primary and secondary outcome

The effect of the family intervention will be measured by self-report questionnaires. The outcome measurements are outlined in Table 2 and will be measured at baseline, post-intervention, and at 6-month follow up (Table 2).

**Table 2 Tab2:** Primary and secondary outcome measures

Domain	Assessment	Test tool (outcome measure)	Administered by
Quality of life (QoL)	Generic QoL	Short Form-36 (SF-36) [9, 10, 52, 53]	All participants
	The patient’s disease-specific QoL	QoL after Brain Injury (Qolibri) [54]	Participants with TBI
		International Spinal Cord Injury QoL Basic Data Set [55]	Participants with tSCI
Self-perceived burden	General burden, isolation, disappointment, emotional involvement, environment	Caregiver Burden Scale (CBS) [12, 56]	Caregivers
	Physical, emotional and financial burden	Self-Perceived Burden Scale (SPB) [57]	Participants with TBI or tSCI
Family dynamic	Flexibility	Family Adaptability and Cohesion Evaluation Scales-IV (FACES-IV) [58]	All participants
	Cohesion		
	Communication		
Problem-solving abilities	Confidence	Problem-Solving Inventory (PSI) [59]	All participants
	Personal control		
	Approach-avoidance		
Mental health	Depression	Patient Health Questionnaire-9 (PHQ-9) [60]	All participants
	Anxiety	Generalized Anxiety Disorder-7 (GAD-7) [61]	
	Satisfaction with life	Satisfaction with Life Scale (SWLS) [62]	
Relationship	Relationship to relatives	Relationship Assessment Scale (RAS) [63–65]	All participants if a dyad
Resilience	Resilience and robustness	The Resilience Scale for Adults (RSA) [66]	All participants

All participants in the two groups will complete self-report questionnaires to collect generic QoL data as the primary outcome measurement, and self-perceived burden, family dynamics, problem-solving strategies, mental health, and resilience as secondary outcome measurements. In cases where the family consists of a dyad, e.g. a married couple, mother and daughter etc., rather than several family members, the Relationship Assessment Scale (RAS) [63–65] will be completed as a supplement.

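### Baseline quality of life is adjusted for only after a significant baseline test, which costs precision and makes the primary model depend on the data

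*Protocol article*

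**What the plan says.** All of this stands in the protocol article. Under Analytical methods, "the baseline level of the primary outcome, generic QoL data, will be compared between groups using one-way analysis of variance (ANOVA"), and the next sentence makes adjustment conditional: "If there are significant differences at baseline, we will adjust for these in the following analyses". No level is given for that test. Other baseline characteristics are handled in the same way: they are compared by one-way ANOVA, and "we will adjust for these characteristics if necessary". No criterion for necessity is given.

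The effect is then examined on an intention-to-treat basis "using repeated measures ANOVA (rANOVA), with “time” as the repeated measurement". The analysis is run within each disease group: "The comparison between the intervention group and control group in each disease group will be the between-group factor".

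The outcomes "will be measured at baseline, post-intervention, and at 6-month follow up" (Primary and secondary outcome), and "Families will complete the baseline questionnaires before randomization" (Implementation and awareness of assignment). The article does not say whether baseline is one of the levels of time, or whether the effect is the group term or the group-by-time term. No other section commits to adjustment in all cases.

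**The concern.** Allocation is random and baseline is recorded first, so a baseline difference between the groups can only be chance. A test of it addresses a hypothesis already known to be true. Whether adjustment helps depends on how strongly baseline predicts the follow-up score, and the p-value does not measure that.

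Two things are at stake. The first is precision: in most trials the test will be non-significant, and the best use of a baseline held for every participant is then forgone. The second is that the primary model is chosen by the data. TBI and tSCI are analysed separately, so by chance one could be adjusted and the other not. If baseline is also a level of time, adding it as a covariate would use it as outcome and predictor at once.

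**Working it through.** **Inputs.** From Sample size: SD 12.5 and a target difference of 5 points on the SF-36 Mental Component Summary (MCS), 80% power, 95% confidence, and 182 participants per disease group, hence 91 per randomised group at 1:1. Assumed, because the article does not give them: a two-sided 0.05 level for the baseline test, a baseline to follow-up correlation r of 0.3 to 0.7, equal SD at each visit, and independent individuals (family clustering ignored).

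**The plan's own figure.** n per group = 2(1.96 + 0.84)² × 12.5² / 5² = 98.1, so 99 per group or 198 per disease group, against 182 stated. An SD of 12.0 gives 90.4, so 91 per group or 182. The stated number therefore does not follow from the quoted SD. That is a separate matter, but it means that at 91 per group and SD 12.5 the unadjusted power is 77.0%, so precision is not in surplus.

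**Imbalance that stays unadjusted.**
- SE of the baseline difference = 12.5 × √(2/91) = 1.85.
- Largest non-significant gap = 1.96 × 1.853 = 3.63 points. This is the limit. The expected absolute gap is about 0.80 × 1.85 = 1.5 points, and a gap between 2 and 3.63 points arises in about 23% of trials.

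**What a gap at the limit does to the result.** If follow-up scores are compared, the shift is r × gap. If change from baseline is compared (a group-by-time contrast), it is (r − 1) × gap, which has the opposite sign.

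| r | Follow-up scores | Change from baseline |
|---|---|---|
| 0.3 | +1.09 | −2.54 |
| 0.5 | +1.82 | −1.82 |
| 0.6 | +2.18 | −1.45 |
| 0.7 | +2.54 | −1.09 |

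**Variance.** Relative to 2σ²/n, the variance of the group difference is 1 for follow-up scores, 2(1 − r) for change, and 1 − r² with baseline as covariate. Change relative to covariate adjustment is thus 2/(1 + r): 1.54 at r = 0.3, 1.33 at 0.5 and 1.18 at 0.7.

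**Power for 5 points (simulated).** The conditional rule was modelled as covariate adjustment when baseline p < 0.05, and otherwise the unadjusted comparison of the score named in the column.

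| r | Always adjust | Conditional, follow-up scores | Conditional, change scores |
|---|---|---|---|
| 0.3 | 80% | 77% | 63% |
| 0.5 | 87% | 78% | 77% |
| 0.6 | 92% | 78% | 86% |
| 0.7 | 96% | 79% | 94% |

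The closed form for always adjusting agrees: 80.7%, 87.6%, 92.1% and 96.5%.

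**Type I error.** About 3.6% to 4.8% under the conditional rule across these settings, against about 5% with adjustment in all cases.

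**The case against.** Several points on the other side stand.

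- A reader might infer that the rule biases the effect estimate. It does not over repeated randomisation; the shifts above describe a particular trial in which a gap has occurred.
- A reader might also infer an inflated false-positive rate. The rule departs from the nominal level, but downwards.
- It would be too strong to say that the baseline information is thrown away. That holds only if follow-up scores are compared. If baseline is a level of time and group-by-time is the effect, baseline is used as a change score: a chance gap is over-corrected rather than left in, and the loss is partial. At r = 0.6 the loss is about 6 percentage points of power rather than 14, and at r = 0.7 about 2. The article's wording permits either reading, so neither set of figures can be given alone.
- The 3.63-point gap is the edge of non-significance; the typical gap is less than half of that.
- The analysts are to be blinded to allocation (Implementation and awareness of assignment; Limitations and generalizability). This limits steering of covariates towards a favourable result, though the model still depends on the data.
- The choice of further covariates is commonly left to the analysis plan, so the vague wording there carries little weight by itself.

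It does not help to say that the whole matter belongs to an analysis plan not shown. The conditional rule is stated in the article, and a later plan could only correct it by departing from it.

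**Conclusion.** The point holds as one about precision and a data-dependent model, and it should be changed. Always adjusting gave more power than the conditional rule under both readings at every correlation examined. The gain over the follow-up-score reading runs from about 3 points (r = 0.3) to 17 points (r = 0.7). Over the change-score reading it runs from about 17 points (r = 0.3) to 2 points (r = 0.7). The validity of the trial is not threatened.

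The figures rest on the assumed correlation, a 0.05 level for the baseline test, 91 per group, SD 12.5, the MCS as the score analysed, and independence of individuals. Because family members are correlated, the absolute power values should be read as a comparison of methods and not as the power of this trial.

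**What to change.** Remove the baseline significance tests as a trigger for adjustment, for the primary outcome and for the other characteristics, and report baseline descriptively by group.

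Within each disease group, adjust for baseline MCS in all cases: model the two post-baseline visits as outcomes with baseline as covariate. A longitudinal model that keeps baseline as an outcome but gives both groups a common baseline mean would serve equally. Either way, baseline is not used both as outcome and as covariate. State which term is the treatment effect, and name any other covariates in advance.

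The cost is more than a single deleted sentence, because the repeated measures ANOVA has to be respecified. No new data are needed, since baseline is already collected from all participants. The change can be made before any comparative analysis; the Trial status section reports only 13 families randomised.

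Suggested wording: *Within each disease group, the MCS at post-intervention and at 6 months will be analysed jointly with baseline MCS as a covariate in all cases. Baseline characteristics will be summarised by group without significance tests.*

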### Sample size

Preliminary statistical power calculations have been carried out to allow us to detect any group effect (intervention versus control in the TBI and tSCI group, respectively) on the primary outcome variable, i.e. generic QoL data assessed by the Short Form-36 (SF-36) [9, 10]. Numbers of participants required in the study were calculated based on the Mental Component Summary (MCS) of the SF-36 [52, 53]. As no studies have been carried out in Denmark using the SF-36 in patients with a traumatic injury, a Norwegian study [70] was used for the sample size calculations. In the Norwegian study, a score of 43.8 (SD 12.5) was reported among patients with moderate to severe TBI. Based on a confidence level of 95%, a power level of 80%, and a significant difference of 5 points between the intervention and control group, it will be necessary to recruit 182 participants to each arm of the trial i.e. the TBI and tSCI arms. To account for a 10% drop-out rate, 400 participants in total must be included.

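### The repeated measures ANOVA names no treatment contrast or primary visit; if its group main effect over all three visits is the test, a sustained 5-point effect shrinks to 3.33

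*Protocol article*

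**What the plan says.** All of the following is in the protocol article.

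- **Model** (Analytical methods): "Intention-to treat (ITT) analyses will be performed to examine the effect of the family intervention using repeated measures ANOVA (rANOVA"), with time as the repeated factor.
- **Treatment term** (same section): "The comparison between the intervention group and control group in each disease group will be the between-group factor". No group-by-time term, post-baseline contrast or primary visit is given.
- **Baseline** (same section): groups are first compared on baseline quality of life by one-way ANOVA, and later analyses are adjusted only if that comparison is significant.
- **Missing data** (same section): Little's MCAR "approach will be applied for analysis of group allocation and of disease group to investigate whether drop-outs or missing data are associated" with these two factors. Nothing follows from the result.
- **Visits**: outcomes are collected at baseline, after the intervention and at 6 months (Primary and secondary outcome). Baseline forms are completed before randomization (Implementation and awareness of assignment). The closing part of the Background names both a short-term and a long-term effect as targets.
- **Sizing** (Sample size): "Based on a confidence level of 95%, a power level of 80%, and a significant difference of 5 points between the intervention and control group". The figure is for the SF-36 Mental Component Summary (MCS), and no visit is attached to the 5 points.

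**The concern.** Naming the factors of a repeated measures ANOVA does not say which term answers the research question. The only term in which the text places the treatment comparison is the between-group factor. Over three visits, that factor averages the group differences at all three. One of those visits precedes randomization, so its expected difference is zero, and the average understates the effect the trial was sized to detect. If the interaction is meant instead, the test is a different one from the two-group difference in the sample size section.

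Baseline adjustment that depends on a significance test also wastes information. Under valid randomization a 5% test triggers it in about 5% of trials, so the gain from a baseline measured on everyone is normally not used.

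Finally, the analysis carries an intention-to-treat label. Classical repeated measures ANOVA on complete cases would exclude randomized participants with a missing visit, and the text does not say whether that is how it will be run.

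At stake are the power of the primary comparison and the freedom to choose among several tests after the data are seen.

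**Working it through.** **Inputs from the document.** Difference 5 points; "a score of 43.8 (SD 12.5) was reported among patients with moderate to severe TBI"; 95% confidence, taken as two-sided 5%; 80% power; "it will be necessary to recruit 182 participants to each arm of the trial i.e. the TBI and tSCI arms", which at 1:1 allocation is 91 per randomized group.

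**Assumed.** Equal correlation r between any two visits, 0.4 to 0.7; equal SD at each visit; no clustering within families; an effect of 5 points at both follow-ups unless stated otherwise.

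**Step 1: the plan's own figure.** n per group = 2 × (1.96 + 0.84)² × (12.5/5)² = 98.1, so 99 per group or 198 per disease group, not 182. An SD of 12.0 gives 90.4, so 91 per group and 182 in all. This mismatch is a separate point. It is why a single follow-up visit, unadjusted, has standard error 12.5 × √(2/91) = 1.853 and power Φ(5/1.853 − 1.96) = 77% rather than 80%.

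**Step 2: group main effect over three visits.** Estimated effect = (0 + 5 + 5)/3 = 3.33, one third lost. If the effect is present at only one follow-up, it is (0 + 5 + 0)/3 = 1.67. The variance factor of a three-visit mean is (1 + 2r)/3, so power = Φ(3.33 / (12.5 × √((1 + 2r)/3 × 2/91)) − 1.96). For r = 0.5 the standard error is 1.513, and 3.333/1.513 − 1.96 = 0.243, giving 60%.

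**Step 3: group-by-time, 2 df.** The visit differences 0, 5, 5 deviate from their mean by −3.33, 1.67 and 1.67, with sum of squares 16.67. Noncentrality = (91/2) × 16.67 / (12.5² × (1 − r)); for r = 0.5 it is 9.71. The F test has 2 and 360 df.

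**Step 4: other comparators.** One follow-up visit with baseline as covariate has variance factor 1 − r². The mean of the two follow-ups without baseline has variance factor (1 + r)/2. Both estimate the full 5 points.

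| Analysis, 91 per group, SD 12.5 | r = 0.4 | 0.5 | 0.6 | 0.7 |
|---|---|---|---|---|
| Group main effect, three visits | 64% | 60% | 56% | 52% |
| Group-by-time, 2 df | 72% | 80% | 88% | 96% |
| Mean of two follow-ups, no baseline | 90% | 88% | 85% | 83% |
| One follow-up visit, baseline as covariate | 84% | 88% | 92% | 97% |

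**Step 5: missing visits.** Little's test is one global comparison of observed values across missingness patterns. It does not isolate an association between drop-out and arm, which is the use the text gives it. A simulation shows what complete-case handling could do. It assumes r = 0.6 and 11 to 12% of 6-month data missing, with drop-out depending on the post-intervention score. Against a true main effect of 3.33, the complete-case value is 3.37 if drop-out works alike in both arms, 2.37 if it is score-dependent in the control arm only, and 1.34 if it runs in opposite directions. These patterns are assumptions; the document gives none.

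**The case against.** The text does not list the levels of time. The clause on adjusting for baseline leaves room for baseline as a covariate with two post-baseline visits, and then nothing is diluted. Nor does naming the design factors exclude the group-by-time term, which is the usual treatment test when baseline is a time level. That test is weaker than the 77% single-visit comparison only at the lowest correlation shown. Detailed handling of missing visits and sensitivity analyses may properly sit in a fuller plan.

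These objections stand, and they rule out three stronger readings that a reader might infer:

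- *The planned test certainly loses a third of the effect.* This holds only if baseline is a time level and the main effect is tested, and neither is stated.
- *The analysis fails to be intention-to-treat.* Complete-case handling is nowhere specified, and some long-format implementations keep participants with a missing visit.
- *The protocol expects drop-out to differ by arm.* Limitations and generalizability only speculates, and it gives a reason for drop-out in each arm. The 10% allowance is already built into the 400 participants.

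The objections do not remove the ambiguity. Unless the baseline test happens to be significant, baseline is either a time level or unused. The interaction test, for its part, does not estimate the difference used for sizing, and neither of the two target times is made primary.

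**Conclusion.** The point holds in conditional form, with medium confidence. The article fixes a model without fixing the test. Across the readings its words allow, power for the same sustained 5-point effect runs from 52% to 96% at 91 per group over assumed correlations of 0.4 to 0.7. On the literal main-effect reading the effect becomes 3.33 and power 64 to 52%. On the interaction reading there is no dilution (72 to 96%), but the result is an omnibus test rather than a two-group difference. Adjusting one stated visit for baseline in every case would give 84 to 97% and estimate the quantity the trial was sized for. These figures rest on equal correlation between visits and ignore clustering within families.

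On missing data, only this is supported: the intention-to-treat label comes with no stated handling of missing visits, and the one step that is stated does not answer the question set for it. Bias from drop-out is possible but not shown.

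**What to change.** Within each disease group, replace the repeated measures ANOVA by a likelihood-based mixed model for the two post-baseline SF-36 MCS scores:

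- baseline MCS always a covariate, not triggered by a significance test;
- arm, visit and arm-by-visit as fixed terms;
- all randomized participants with any follow-up included;
- one primary contrast, the arm difference at one stated post-baseline visit, with the other visit secondary.

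Replace Little's test by a direct comparison of drop-out by arm and disease group.

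The cost is a small change to the analysis wording and standard Stata mixed-model code, with no change to data collection. The model relies on data being missing at random, which should be stated. Further sensitivity analyses can be left to the full analysis plan.
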